### Referral and recruitment

The first recruitment strategy is via secondary mental healthcare facilities. Patients who are currently treated for depression with cognitive therapy will be informed by their therapist about this study. Patients will also be offered written information by either a research associate or via e-mail or post. Secondly, patients who have been treated for depression with A-CT in the past will be informed through their former mental healthcare facility. They will receive written information about the study and a request to sign the informed consent. The third recruitment strategy is via media. The study will be promoted through press releases to local media, advertisements and digital online promotions using the study’s website. If someone is interested in participating, s/he can contact the researcher by e-mail, phone or through the website.

### Informed consent

We inform patients about the study before they sign informed consent. They will receive a letter containing all the information and a digital informed consent. If they agree to enter the trial, they fill out the digital informed consent and then are contacted by a researcher for the baseline assessment.

Approval of the Stichting Medisch-Ethische Toetsingscommissie Instellingen Geestelijke Gezondheidszorg (METiGG) is obtained and the trial is conducted in compliance with the Declaration of Helsinki [25].

### Inclusion criteria

We will include patients:with at least two previous depressive episodeswho are currently in remission according to DSM-IV criteria, for at least two months as assessed by the Structured Clinical Interview for DSM-IV Axis I Disorders (SCID-I)with none to mild depressive symptoms defined as a current score of <14 in the 17 item Hamilton Depression rating scalewho have received A-CT, with a minimum of eight sessionswho are fluent in Dutch

### Exclusion criteria

We exclude patients who have:current mania or hypomania or a history of bipolar illness, any psychotic disorder (current and previous)current alcohol or drugs misuseacute predominant anxiety disorder

There are no restrictions with respect to co-morbidity on Axis II and III, in exception of a concurrent chronic somatic illness that is as risk factor for relapse and recurrence.

### Withdrawal

Participants can withdraw from treatment or from the study at any time. If they decide to withdraw from the trial treatment we ask them whether they are willing to finish the remaining assessments.

### Assessment of eligibility and baseline measures

After filling in the informed consent participants are contacted by a researcher for baseline assessment. This assessment is done at the secondary care facility, by phone or at the participant’s home, depending on their preference. The researcher will check for potential inclusion and exclusion criteria through an initial screening. They will start the baseline assessment using the Structured Clinical Interview for DSM-IV Axis I Disorders (SCID-I) [26] and Hamilton Depression rating scale (HAM-D) [27]. Afterwards the researcher contacts the primary investigator to evaluate the participant and decide whether the participant can participate in the study. If the participant cannot participate in the study, s/he will be contacted by the researcher. If the participant is eligible to participate in the study, s/he will be contacted by the primary investigator to receive the allocation. They will also receive the self-report measures completing the baseline measure by e-mail. After 3 months, all participants received a one year magazine subscription. For a complete overview of the procedure see Fig. 1.

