### Outcome measures/Instruments

Every participant will be monitored over a period of 15 months. After baseline assessment, follow up assessments of patients in the TAU condition will be performed at 1, 2, 3, 6, 12 and 15 months. Patients in the experimental condition will be assessed every session and after 3, 6, 12, and 15 months. The assessments done at baseline and at 15 months consist of an interview and self-report measures. Al interviews will be performed by trained assessors. The assessors are blind to the allocation of the participants. The remaining assessments are self-report questionnaires, which are filled in by the patients and their therapists. For an overview of the assessments at baseline, post treatment and follow up see Table 1. For an overview of the assessments after each session see Table 2.

**Table 1 Tab1:** Overview of assessments

Measure	Description	T0	T1	T2	T3	T4	T5	T6^a^
Interviews								
SCID-I	DSM-IV-TR Axis I disorders	x						x
HAM-D	Depressive symptoms and severity	x						x
Self report measures								
IDS-SR	Depressive symptoms	x			x	x	x	x
IIP-C	Social and interpersonal functioning	x						
EQ-5D	Quality of life	x			x	x	x	x
TIC P	Direct/indirect costs	x			x	x	x	x
PMS	Psychological mindedness	x				x		
PDQ-4	Personality				x			
Brugha	Life events	x						x
EPCL	Everyday problems	x				x	x	
Mastery scale	Mastery	x			x	x	x	x
VAMS	Mood	x			x	x	x	x
IVM	Victimization							x
SSL-I	Social support		x	x	x	x		x
UCL	Coping		x	x	x	x		x
AAQ	Experiential acceptance and avoidance		x	x	x			
ORS	Functioning		x	x	x			
Affiliation	Affiliation		x	x	x			
PANAS-X	Emotions		x	x	x			
DAS	Dysfunctional attitudes		x	x	x		x	
BDI	Depressive symptoms		x	x	x			

^a^T0 = Baseline, T1 = 1 month, T2 = 2 months, T3 = 3 months, T4 = 6 months, T5 = 12 months, T6 = 15 months

**Table 2 Tab2:** Overview of assessments after each session

Measure	Description	S1	S2	S3	S4	S5	S6	S7	S8^a^
UCL	Coping	x		x		x		x	
SSL-I	Social support		x				x		
AAQ	Experiential acceptance and avoidance		x				x		
ORS	Functioning	x	x	x	x	x	x	x	x
SRS	Session evaluation		x		x		x		x
BDI	Depressive symptoms	x		x	x	x		x	x
WAI-SR	Therapeutic relationship		x		x		x		x
DAS-17	Dysfunctional attitudes	x	x	x	x	x	x	x	x
Affiliation	Affiliation		x		x				x
Daily h.	Daily stressors	x		x		x		x	
PANAS	Emotions	x	x	x	x	x	x	x	x

^a^S = session number

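### The T0 self-report questionnaires are sent with or after disclosure of the allocation, so they are not assured to be pre-randomisation values for the secondary and economic analyses

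*Protocol article*

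**What the plan says.** The order of events is in the protocol article, Assessment of eligibility and baseline measures. After consent, a researcher carries out the SCID-I and HAM-D. Next comes the eligibility decision: "Afterwards the researcher contacts the primary investigator to evaluate the participant and decide whether the participant can participate in the study". For an eligible participant the text continues: "s/he will be contacted by the primary investigator to receive the allocation". The following sentence reads: "They will also receive the self-report measures completing the baseline measure by e-mail".

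Table 1, under Outcome measures/Instruments, treats these questionnaires as baseline. It defines T0 as baseline and marks, for example, "IDS-SR Depressive symptoms x", "EQ-5D Quality of life x" and "TIC P Direct/indirect costs x" in the T0 column. IIP-C, PMS, Brugha, EPCL, the Mastery scale and VAMS are also marked there.

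The same section says of the interviews: "The assessors are blind to the allocation of the participants". No blinding of participants is described, and with PCT added to TAU against TAU alone they will know their arm.

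**The concern.** A baseline value is protected by randomisation only if it is fixed before the participant can react to the allocation. Here the participant may rate mood, quality of life, mastery and everyday problems already knowing whether PCT will be offered. Hope in one arm or disappointment in the other could move the scores. It could also affect who returns the forms. Either would produce a difference between arms at T0 that is neither chance imbalance nor an effect of the therapy sessions.

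The scores at risk have real uses. IDS-SR and EQ-5D are secondary outcomes. T0 EQ-5D is the first point of the QALY curve in the cost-utility analysis. T0 TIC-P is the baseline cost measure. IIP-C is measured only at T0, and PMS and Mastery are also measured there. All three are listed under Other parameters as candidate moderators, mediators or mechanisms of change.

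**Working it through.** **Step 1: sequence.** This is a question of order, and the plan has no figure to reproduce.

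| Step in the text | Measures collected | Position relative to allocation |
|---|---|---|
| Interview | SCID-I, HAM-D | Before |
| Eligibility decision | none | Before |
| Contact by the primary investigator | none | Allocation disclosed |
| E-mailed self-report set | IDS-SR, IIP-C, EQ-5D, TIC-P, PMS, Brugha, EPCL, Mastery, VAMS | With or after disclosure |

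The set is described as completing the baseline, so the baseline is unfinished when the allocation is given. Randomisation must already have taken place by then. BDI, UCL, SSL-I and DAS have no T0 mark and are outside the point.

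**Step 2: which analyses use these scores** (section Analysis).

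- Primary Cox model: the event is SCID-I relapse or recurrence. The covariates are number of episodes, time since previous episode and time since last treatment. No T0 questionnaire enters.
- Mixed models: the only named covariate is number of episodes. T0 matters if it enters as first repeated measure or as an added covariate. A shift d confined to T0 would bias a change-from-baseline contrast by -d, and a baseline-adjusted contrast by -b x d, where b is the regression slope on baseline. The documents give neither d nor b.
- Economic evaluation: T0 utility enters the QALY by linear interpolation.

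**Step 3: size for the QALY.** Table 1 marks EQ-5D at 0, 3, 6, 12 and 15 months. The interpolation weights, in years, are:

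- T0: (3/12)/2 = 0.125
- 3 months: (3 + 3)/24 = 0.25
- 6 months: (3 + 6)/24 = 0.375
- 12 months: (6 + 3)/24 = 0.375
- 15 months: (3/12)/2 = 0.125

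They sum to 1.25 years, of which 1.125 belongs to follow-up.

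Assumptions, none of them from the documents: a reporting shift d = 0.03, higher in PCT and present at T0 only; equal utility variances at all visits; a common correlation rho of 0.3 to 0.7 between baseline and later utility.

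- Unadjusted bias: 0.125 x d = 0.125 x 0.03 = +0.004.
- Slope of QALY on T0 utility: 0.125 + 1.125 x rho.
- Baseline-adjusted bias: 0.125d - (0.125 + 1.125 x rho)d = -1.125 x rho x d.

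| rho | Slope | Adjusted bias for d = 0.03 |
|---|---|---|
| 0.3 | 0.46 | -0.010 |
| 0.5 | 0.69 | -0.017 |
| 0.7 | 0.91 | -0.024 |

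The two biases have opposite signs. Without adjustment the shift slightly favours PCT; with adjustment it works against PCT, and by more.

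**The case against.** The strongest reply is that the main result is safe, and that stands. The primary outcome comes from blinded interviewers, the Cox covariates are not questionnaire scores, the T0 HAM-D precedes allocation, and so does the stratification variable. A reader might infer that the trial's baseline as a whole, or its primary comparison, is compromised. The documents do not support that.

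A second reply is that the larger biases belong to analyses the article does not specify. This also stands in part. The article names no baseline-score covariate for the mixed models, no change-score contrast and no adjustment for baseline utility. Those biases are therefore conditional. The T0 value nevertheless enters the QALY in any case.

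Third, most moderators named under Analysis are not exposed. Gender, the illness-history items and antidepressant use are not reactive scales. Residual symptoms can be taken from the pre-allocation HAM-D, and coping (UCL) has no T0 mark. The point is confined to candidates such as IIP-C, PMS and Mastery.

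Fourth, the size of any shift is unknown, and a shift that persisted equally at follow-up would cancel in change scores. A reader might also conclude that baseline data will be missing by arm. Differential return is a risk created by the sequence, not something the documents show.

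Finally, the wording fixes no interval between the allocation contact and the e-mail, and Fig. 1, cited for the full procedure, is not shown. That lowers confidence. It does not reverse the reading, because no visible text places the forms earlier.

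**Conclusion.** The point holds for the T0 self-report set only. On the stated sequence these scores are collected with or after disclosure from unblinded participants, so they cannot be assumed to be pre-randomisation values, and completion may differ by arm. The risk falls on secondary and economic analyses that use them as first repeated measure, covariate, moderator or QALY anchor.

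Under the stated assumptions, a 0.03 utility shift confined to T0 biases the 15-month QALY difference by about +0.004 unadjusted and by about -0.010 to -0.024 after baseline adjustment. A reader might multiply the whole slope by 0.03 and obtain 0.014 to 0.027. For a reporting shift confined to T0 that overstates the bias, because the shifted T0 value also enters the QALY itself, with weight 0.125 and the opposite sign.

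This should be fixed, but it does not threaten the primary conclusion. Confidence is moderate, because Fig. 1 is not shown.

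**What to change.** **For participants not yet allocated:** send the T0 self-report set after the SCID-I/HAM-D interview and the eligibility decision. The independent researcher, who according to the Design section alone has access to the randomisation, should release the allocation only once the set is returned or a short time limit has passed. Mark any T0 form completed after disclosure.

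**For participants already allocated** (the article describes one procedure in the past tense, so recruitment may be under way):

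- record the T0 completion date relative to disclosure and report return rates by arm;
- describe these scores as post-randomisation;
- run sensitivity analyses with the pre-allocation HAM-D as severity baseline, omitting post-allocation T0 scores as covariates or moderators.

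**Cost:** allocation may be delayed by a few days. No measures or staff are added. The sensitivity analyses use data already planned, plus the completion and disclosure dates. Pre-allocation values that were not collected cannot be recovered later.

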### Outcome measures/Instruments

Every participant will be monitored over a period of 15 months. After baseline assessment, follow up assessments of patients in the TAU condition will be performed at 1, 2, 3, 6, 12 and 15 months. Patients in the experimental condition will be assessed every session and after 3, 6, 12, and 15 months. The assessments done at baseline and at 15 months consist of an interview and self-report measures. Al interviews will be performed by trained assessors. The assessors are blind to the allocation of the participants. The remaining assessments are self-report questionnaires, which are filled in by the patients and their therapists. For an overview of the assessments at baseline, post treatment and follow up see Table 1. For an overview of the assessments after each session see Table 2.

**Table 1 Tab1:** Overview of assessments

Measure	Description	T0	T1	T2	T3	T4	T5	T6^a^
Interviews								
SCID-I	DSM-IV-TR Axis I disorders	x						x
HAM-D	Depressive symptoms and severity	x						x
Self report measures								
IDS-SR	Depressive symptoms	x			x	x	x	x
IIP-C	Social and interpersonal functioning	x						
EQ-5D	Quality of life	x			x	x	x	x
TIC P	Direct/indirect costs	x			x	x	x	x
PMS	Psychological mindedness	x				x		
PDQ-4	Personality				x			
Brugha	Life events	x						x
EPCL	Everyday problems	x				x	x	
Mastery scale	Mastery	x			x	x	x	x
VAMS	Mood	x			x	x	x	x
IVM	Victimization							x
SSL-I	Social support		x	x	x	x		x
UCL	Coping		x	x	x	x		x
AAQ	Experiential acceptance and avoidance		x	x	x			
ORS	Functioning		x	x	x			
Affiliation	Affiliation		x	x	x			
PANAS-X	Emotions		x	x	x			
DAS	Dysfunctional attitudes		x	x	x		x	
BDI	Depressive symptoms		x	x	x			

^a^T0 = Baseline, T1 = 1 month, T2 = 2 months, T3 = 3 months, T4 = 6 months, T5 = 12 months, T6 = 15 months

**Table 2 Tab2:** Overview of assessments after each session

Measure	Description	S1	S2	S3	S4	S5	S6	S7	S8^a^
UCL	Coping	x		x		x		x	
SSL-I	Social support		x				x		
AAQ	Experiential acceptance and avoidance		x				x		
ORS	Functioning	x	x	x	x	x	x	x	x
SRS	Session evaluation		x		x		x		x
BDI	Depressive symptoms	x		x	x	x		x	x
WAI-SR	Therapeutic relationship		x		x		x		x
DAS-17	Dysfunctional attitudes	x	x	x	x	x	x	x	x
Affiliation	Affiliation		x		x				x
Daily h.	Daily stressors	x		x		x		x	
PANAS	Emotions	x	x	x	x	x	x	x	x

^a^S = session number

### Primary outcome

The primary outcome measure will be the cumulative proportion of relapse or recurrence of depression meeting DSM-IV criteria for a major depressive episode according to the Structured Clinical Interview for DSM-VI Axis I Disorders (SCID-I) over a follow-up period of 15 months.

### Secondary outcome

Secondary outcome variables are;Depressive symptom severity as measured with the HAM-D [27], Inventory of Depression Symptomatology (IDS) [28] and the Beck Depression Inventory (BDI-II) [29].Duration of relapse/recurrence.Number of relapses.Quality of life as measured by the EuroQol (EQ-5D). The EQ-5D scores will be used to calculate utilities using the Dutch tariff [30]. Quality-adjusted life-years (QALYs) will be calculated by multiplying the utility of a health state by the time spent in this health state using linear interpolation between time points. Higher QALY scores indicate higher quality of life.Health care utilization and productivity losses will be measured with an adapted version of the Trimbos Questionnaire for Costs associated with Psychiatric illness (TIC-P), a widely used health service receipt interview in economic evaluations [31]. Costs that will be included in the economic evaluation are direct medical and non-medical costs, and indirect costs. Resource utilization (GP visits, hospital days, ect.) will be valued using Dutch standard costs [32]. Using the TiC-P, both absenteeism and presenteeism (working less efficiently while at work) will be measured. Productivity losses will be valued using the friction cost method.The frequency and intensity of daily stress as measured with the Brugha and the Everyday Problem Checklist (EPCL) [33].

### Other parameters

As potential moderators, mediators and mechanisms of change we will analyze; personality traits measured by the Personality Diagnostic Questionnaire (PDQ-4) [34], psychological mindedness measured by the Psychological Mindedness Scale (PMS) [35], mastery measured by the Mastery scale [36], social support measured by the Sociale Steun Lijst (SSL-I) [37], coping measured by the Utrechtse Coping Lijst (UCL) [38], experiential acceptance and avoidance measured by the Acceptance and Action Questionnaire (AAQ-II) [39], functioning measured by the Outcome Rating Scale (ORS) [40], affiliation measured by the Affiliation scale [41], emotions measured by the Positive and Negative Affect Schedule (PANAS-X) [42], dysfunctional attitudes measured by the Dysfunctional Attitude Scale (DAS) [43, 44], social en interpersonal functioning measured by the Inventory of Personal Problems (IIP-C) [45], depressive mood measured by a one item mood scale [46], session evaluation measured by the Session Rating Scale (SRS) [47], therapeutic relationship measured by the Working Alliance Inventory-Short Revised (WAI-SR) [48], mood measured by a one-item Visual Analogue Mood Scale (VAMS) [46] and Victimisation measured by the Dutch version of the Integral Safety/Security Monitor (IVM) [49].

### Analysis

The primary outcome measure will be the time to relapse or recurrence meeting DSM-IV criteria for a major depressive episode on the Structured Clinical Interview for DSM-VI (SCID-I). Occurrence of relapse or recurrence (current or since the last assessment point) will be assessed after 15 months, by trained psychologists who are blind to the treatment condition. Cox regression analysis will be performed. Analysis will be conducted by intention to treat, including all subjects randomized in the study, and per protocol. Statistical significance will be set at p < .05. The time (in weeks) of relapse or recurrence to Major Depression, as defined above, will be the dependent variable in survival analysis. The treatment group will be used as predictor, and the stratification variable will be used as covariate. In addition, time since previous episode and time since last treatment will be included as covariates.

In addition, we use the HAM-D, to assess the severity of depression at both time points, together with the SCID-I.

Mixed-model analysis will be used for the quantitative measures. As covariates we will use the stratification variable (number of episodes). Potential moderators to be examined include gender, residual symptoms of depression, duration of remission, duration of last episode, coping, age of onset and current use of AD.

For the economic evaluation the relationship between costs and health outcomes of the two treatment conditions will be evaluated using a societal perspective. Both a cost-effectiveness analysis with depression-free survival time as effect measure and a cost-utility analysis with QALYs as effect measure will be performed.

The economic evaluation will be done according to the intention-to-treat principle. Incremental cost-effectiveness ratios (ICERs) will be calculated by dividing the difference in mean total costs between the treatment groups by the difference in mean effects between the treatment groups. Bootstrapping with 5000 replications will be used to estimate 95 % confidence intervals around cost differences and the uncertainty surrounding the ICERs. Rubin’s rules will be used to pool the results from the different multiply imputed datasets. Uncertainty surrounding the ICERs will be graphically presented on cost-effectiveness planes. Cost-effectiveness acceptability curves showing the probability that the intervention is cost-effective in comparison with usual care for a range of different ceiling ratios will also be estimated [50].

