## Background

High prevalence, and frequent relapse and recurrence contribute to the public health significance of Major Depressive Disorders (MDD). Depression is the most disabling disorder worldwide measured in years lived with disability [1]. In various recent epidemiological studies, the annual prevalence in the general population varies from 4 % to 6 % [2, 3]. Epidemiological estimates place the lifetime prevalence of MDD at more than 16 % [4]. However, the major contribution of MDD to disability and health care costs is largely due to its highly recurrent nature. The large majority of individuals with MDD experience more than one episode and the probability of another episode increases with each relapse or recurrence [5, 6]. Reported relapse and recurrence rates for high risk groups, rise up to 60–70 % recurrence over 2 year [7, 8]. Apart from the number of previous episodes, residual symptoms after remission are risk factors for recurrence [9, 10]. Optimizing long-term outcomes is therefore an important goal in the treatment of MDD, especially for well-known high risk groups, i.e. patients with multiple previous episodes and/or residual symptoms.

We know that acute phase treatment of depression with Cognitive Therapy (A-CT) has a prophylactic effect [11]. After completing A-CT, patients are less likely to relapse than after stopping a similar course of pharmacotherapy [12]. However, recent meta-analysis showed that after remission on A-CT, many responders still have a relapse-recurrence (29 % within 1 year and 54 % within 2 years) [8]. Other studies also show that after remission a sizable number (40 %) will experience a return of symptoms after treatment [9, 13].

The most commonly used treatment to prevent relapses and recurrences is antidepressant medication (AD). However, 70–80 % of patients are not willing to take AD for a long period of time [14, 15]. Also non-adherence is common among AD-users, which is troubling as patients’ protection from recurrence ceases on discontinuation of AD and therefore increases the risk of recurrence [16, 17]. Most patients prefer psychological interventions to drug treatment, this is especially relevant in long term treatment as studies show that patients’ treatment preference is associated to compliance [18].

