### Sample size

In total, 214 patients will be recruited. This sample size is needed to detect a difference in the primary outcome (cumulative proportion of relapse/recurrence rates over 15 months) of at least 20 % between the conditions in a 1-sided test at alpha = 0.05 and a power of (1-beta) = 0.80. For this we need 85 participants in each condition. Allowing for a drop out of 20 % over the two years, we need to include 107 participants in each condition at baseline.

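### The primary Cox model does not adjust for baseline residual symptoms, which the protocol itself names as a risk factor; adding baseline HAM-D would gain a modest amount of power at no data cost

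*Protocol article*

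**What the plan says.** All references are to the protocol article.

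- **Risk factors (Background).** "Apart from the number of previous episodes, residual symptoms after remission are risk factors for recurrence". The same section counts patients with several earlier episodes and/or residual symptoms as the high-risk groups.
- **Primary model (Analysis; Treatment as usual).** Weeks to relapse or recurrence are analysed by Cox regression. "The treatment group will be used as predictor, and the stratification variable will be used as covariate". Two further covariates follow: elapsed time from the last episode and elapsed time from the last treatment. The Treatment as usual section adds a covariate for the care a patient received within TAU.
- **Role of residual symptoms (Analysis).** They appear once, in the list of potential moderators.
- **Balance and availability.** The Design section stratifies on number of episodes only. Entry requires a HAM-D below 14. Table 1 has HAM-D at T0, and the section on eligibility and baseline measures places this interview before the eligibility decision and allocation.
- **Economic evaluation (Analysis).** The ICER is obtained "by dividing the difference in mean total costs between the treatment groups by the difference in mean effects between the treatment groups". No baseline covariate is named. Table 1 has EQ-5D and TIC-P at T0.

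**The concern.** The covariate list for the primary model is written out, so this is a stated choice and not a gap left to a fuller plan. It takes in several other patient characteristics and omits one of the two risk factors that the Background puts first. Neither stratification nor the model covers it.

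A prognostic baseline covariate in a Cox model brings power and removes the effect of chance imbalance on that factor. Leaving it out forgoes both. If the investigators notice an imbalance in residual symptoms only after the data are in, adding HAM-D then would be an unplanned change to the primary analysis.

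A lesser question of the same kind arises for QALYs. T0 utility is part of each patient's area under the utility curve, so a chance difference at baseline passes into the QALY difference unless it is adjusted for.

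**Working it through.** **1. The plan's own sample size.** Inputs from the Sample size section: a 20-point difference, tested "in a 1-sided test at alpha = 0.05 and a power of (1-beta) = 0.80"; "For this we need 85 participants in each condition"; 20% dropout. The two arm rates are not given. Taking 54% (the two-year relapse figure in the Background) versus 34% as an assumption:

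- n = [1.645 × √(2 × 0.44 × 0.56) + 0.842 × √(0.54 × 0.46 + 0.34 × 0.66)]² / 0.20² = 75.1.
- With continuity correction: (75.1/4) × [1 + √(1 + 4/(75.1 × 0.20))]² = 84.8, so 85 per arm.
- 85/0.80 = 106.25, so 107 per arm and 214 in total.

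The stated figures reproduce, and they do not depend on covariate adjustment.

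**2. Power with and without baseline symptoms.** The protocol does not give the strength of the relation between symptoms and relapse, so it is varied. Set-up: 85 per arm; exponential times with hazard exp(L + ln(HR) × x), where x is a standardised baseline symptom score; L is set in each arm so that the 15-month risk averaged over x is 60% (TAU) or 40% (PCT); one-sided 5% test; 3,000 trials per row for power and 2,000 for type I error. At these risks the marginal treatment hazard ratio is ln(0.60)/ln(0.40) = 0.557.

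| Assumed HR per SD of symptoms | Power without | Power with | Gain (points) | Type I error without / with |
|---|---|---|---|---|
| 1.25 | 84.9% | 85.8% | 0.9 | 5.35% / 4.90% |
| 1.50 | 85.4% | 88.0% | 2.7 | 4.85% / 4.95% |
| 1.75 | 85.0% | 90.8% | 5.8 | 4.40% / 4.75% |
| 2.00 | 85.2% | 92.1% | 7.0 | 5.00% / 4.80% |

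Gains are taken from unrounded powers. The simulation standard error of one power figure is √(0.85 × 0.15/3000) = 0.65 points, and of one type I error figure √(0.05 × 0.95/2000) = 0.49 points. Type I error is therefore compatible with 5% in every row. The mean estimated treatment hazard ratio at the strongest relation is 0.553 without and 0.505 with the covariate.

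**3. QALYs (illustration only).** EQ-5D is taken at 0, 3, 6, 12 and 15 months, so under linear interpolation T0 has weight 1.5 months = 0.125 years and the later values share 1.125 years. The utility SD (0.20) and the correlation r of T0 with later values (0.3 to 0.7) are assumptions; the SD is taken as equal at all visits.

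- SE of the baseline utility difference: 0.20 × √(2/107) = 0.0273.
- QALY shift per unit of baseline difference: 0.125 + 1.125r = 0.46 to 0.91.
- A one-SE chance imbalance shifts the QALY difference by 0.0273 × 0.46 to 0.0273 × 0.91 = 0.013 to 0.025.

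**The case against.** - **The planned Cox test is sound without this covariate.** This stands. Pre-specifying the stratification factor and some other variables, and examining residual symptoms as a moderator, is defensible. The hazard ratio nearer to 1 in the unadjusted fit is a marginal effect and not a wrong one. The point is about efficiency only.
- **The gain may be smaller than shown.** This also stands. The simulation compares a model with treatment alone to one with treatment and symptoms. The planned model already has other covariates, and if these correlate with symptoms the increment shrinks. The entry limit on HAM-D narrows the covariate's range too.
- **A reader might infer that the trial is already near or below 80% power.** The Sample size section uses a one-sided test, and on that basis power is about 85% in the 60/40 scenario. Power falls below 80% there (about 75% by a test of two proportions) only if the significance level in the Analysis section is read as two-sided. That section does not say, and sidedness is a separate matter.
- **A reader might take a hazard ratio of about 2.6 for residual symptoms from the Background**, from 62% versus 31% relapse: ln(0.38)/ln(0.69) = 2.61. The 62% belongs to patients with unstable remission. For residual symptoms the Background gives no rates.
- **A reader might infer that the ICER uses unadjusted means.** The text gives the general definition of an ICER, which adjusted means also satisfy, in a condensed article that likewise omits its imputation model. Silence here does not establish an error.
- **A reader might extend the remedy to a T0 value in every mixed model.** Table 1 has no T0 value for the BDI, a named secondary outcome, so this cannot be done across the board.

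**Conclusion.** The point holds for the primary Cox model. The stated covariates leave out a baseline risk factor that the protocol names, that randomisation does not balance by design, and that is measured before allocation. On the assumptions of 60% versus 40% relapse, 85 per arm, a one-sided 5% test and a hazard ratio of 1.25 to 2.0 per SD, adding it is worth roughly 1 to 7 points of power above a base of about 85%. Nothing shows inflated type I error, systematic bias or power below the planned 80% as a result of the omission.

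The economic part is secondary. The mechanism is real, but it concerns chance imbalance and precision, its size rests on an assumed SD and correlation, and the article does not rule out adjustment. There is also an obstacle: the section on eligibility and baseline measures describes e-mailing the T0 self-report forms only after describing the contact about allocation, so EQ-5D and TIC-P may be answered with allocation known. In that case T0 utility and costs would not be clean baseline covariates.

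**What to change.** **Main change.** In the Analysis section, add T0 HAM-D as a continuous covariate in the primary Cox model, fixed before outcome data are examined, and keep residual symptoms as a moderator in a separate analysis. The cost is one sentence. The score is part of the eligibility check, so it should be available for every randomised patient.

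**Optional change.** If the full plan does not already do so, estimate incremental QALYs and costs by regression on treatment group with T0 utility and T0 costs, inside the planned bootstrap and imputation. This is appropriate only if the T0 self-report forms are completed before allocation is disclosed. If they are currently sent with or after the allocation, this is a change of procedure and not of wording alone; the baseline section should state the order either way.
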